### Index:

|  | Page |
| --- | --- |
| 1. EXECUTIVE SUMMARY | 4 |
| 2. BACKGROUND AND CURRENT STATUS OF THE ISSUE. | 5 |
| 3. OUTCOMES | 7 |
| 4. RESEARCH METHODOLOGY | 7 |
| - Study design | 7 |
| - Target population and study groups | 8 |
| - Selection process and screening invitation. | 8 |
| - Study variables and procedures. | 9 |
| - Statistical analysis and sample size calculation | 10 |
| - Cost and cost-effectiveness analysis. | 10 |
| 5. EXPECTED RESULTS | 11 |
| 6. RESEARCH GROUP EXPERIENCE AND SUITABILITY. | 12 |
| 7. WORKPLAN AND SCHEDULE | 12 |
| 1. COMMUNICATION, DIFFUSION AND APPLICATION OF RESULTS 2. AMENDMENTS | 13  14 |

1. **EXECUTIVE SUMMARY**

**Background:** Colonoscopy is the gold standard procedure for CRC screening in the familial-risk population. However, the efficacy of screening in first-degree relatives (FDR) of patients with colorectal cancer (CRC) is limited by a poor adherence (<50%). Recently it has been suggested that annual fecal immunochemical testing (FIT) is equivalent to colonoscopy for the detection of advanced colorectal neoplasia, if would have the capacity to improve colonoscopy uptake.

**Outcomes:** the primary outcome is to compare screening uptake of annual fecal immunochemical testing (FIT) versus one-time colonoscopy in individuals with a high-risk family history of non- syndromic CRC. Secondary outcomes: 1) to compare the efficacy of annual FIT vs direct colonoscopy for detecting advanced colorectal neoplasia (ACN: advanced adenoma, advanced serrated polyp or CRC) in this population. 2) to determine the cost-effectiveness of both strategies.

**Methodology:** This is a multicentre (12 hospitals), randomized, open-label, parallel group, phase III controlled trial. Inclusion criteria:

1. Having a high-risk family history of CRC: must meet one of the following conditions; a) at least one FDR index case of CRC at <60 years old; b) two FDR diagnosed with CRC, regardless of age at diagnosis; or c) to have a sibling with CRC, regardless of age at diagnosis;
2. Asymptomatic individuals over 40 years old or 10 years younger than the FDR index case when diagnosed with CRC, if the index case was <50 years old.
3. Histologically confirmed CRC in the index case.

Exclusion criteria: prior screening, personal history of ACN, hereditary CRC syndrome, abdominal symptoms needing further investigation or severe comorbidity.

Study groups: 1) annual FIT over three years (cutoff ≥ 10 μg Hb/g faeces to indicate colonoscopy); and

2) straightforward colonoscopy.

The recruitment process will be programmed through the index case, that will be interviewed to obtain their CRC family history. FDR will be contacted to make an appointment in the High-risk CRC Clinic of the participant centres. Randomization (1:1) will be performed before signing the informed consent to avoid selection bias. A researcher will be responsible to provide detailed information about the study and getting the informed consent. In case of willingness to participate in the study, the FDR will be randomized to one of the following arms: A) One-time colonoscopy; B) annual FIT (Automated quantitative Fecal Immunochemical Test) for three screening rounds and a colonoscopy in case of a positive FIT (cut-off = 10 μg Hb/g faeces). Screening uptake will be defined as the percentage of FDR who participate at least in one of the three FIT screening rounds in the FIT group or who undergo colonoscopy in the other group. Screening uptake will be calculated under the assumption of intention to screen analysis. Detection rates of advanced colorectal neoplasia will be assessed by as-screened analysis.

Sample size calculation

Assuming adherence rates of 0.60 vs 0.50 for FIT and colonoscopy, respectively, an alpha risk = 0.05, a beta risk = 0.10, in two-side tails, 538 FDR are required per group. The recruitment process will be programmed through the index case.

### BACKGROUND AND CURRENT STATUS OF THE ISSUE.

Colorectal cancer (CRC) is the most common malignant tumor in Spain with over 30,000 new cases per year and is the second leading cause of cancer mortality in the country with over 14,000 deaths per year [1]. Survival in patients with CRC depends on the disease stage at diagnosis. If detected at an early stage, treatment is curative in nearly 100% of cases, whereas <10% of patients with metastatic CRC survive for more than 5 years [1]. Family history is, with age, the most important risk factor in CRC development. The risk of developing CRC is almost doubled (RR 1.82; 95% CI 1.47, 2.25) in first- degree relatives (FDRs) of patients diagnosed with CRC when over 60 years old. This risk is increased if the index case is less than 60 years old at diagnosis (RR 2.25; 95% CI 1.85, 2.72) or people have two or more FDRs with CRC (4.25; 95% CI 3.01, 6.02) [2]. In addition, it has been recently found that the risk of advanced adenoma is up to three times higher (OR 3.07; 95% CI 1.5, 6.3) among siblings of patients with CRC than among siblings of subjects without CRC [3].

Currently, colonoscopy is the most widely used method for CRC screening in the familial risk population, as it allows both diagnosis and treatment of premalignant lesions (advanced adenomas) by performing polypectomy. Clinical practice guidelines recommend colonoscopy every 5 years, from the age of 40 or ten years less than the youngest relative at CRC diagnosis [4,5]. This strategy greatly reduces the risk of CRC development in FDRs of a patient previously diagnosed with CRC [6]. However, there are no clinical trials comparing the efficacy of colonoscopy screening with other screening strategies.

Despite being the most widely used screening method in the population at familial risk, colonoscopy has numerous drawbacks. Firstly, between 20-26% of adenomas of any size and up to 6-12% of advanced lesions may be missed. Secondly, it is an expensive procedure that requires intravenous sedation and staff training. Thirdly, it is an invasive technique with risks of serious complications, although these are infrequent. Endoscopic polypectomy has a global rate of post-polypectomy bleeding or intestinal perforation of 0.26% and 0.04% of procedures, respectively [7]. However, risk of complications increases significantly if the polyp is located in the cecum or if the polyp is >20 mm in diameter [8]. Furthermore, beneficial effect of colonoscopy to reduce the incidence and mortality rates of CRC is significantly lower in tumors located in the right colon than in those located in the left colon [9]. Finally, its efficacy as a screening test in FDRs of patients with CRC is limited by poor adherence. Population studies conducted in Spain and Australia have found that only 38% and 20% of FDRs, respectively, receive a screening colonoscopy following the recommended timelines given by clinical practice guidelines [10,11].

Several studies have shown that screening by annual or biennial fecal occult blood test (FOBT) reduces CRC incidence and mortality in the average risk population, which consists of asymptomatic persons

≥50 years old with no family history of the disease [12]. In addition, a Spanish multicentre study in this same population showed that immunochemical fecal occult blood test (FIT) was better accepted than colonoscopy and showed a similar CRC detection efficacy [13]. These satisfactory FIT performance results in the average-risk population suggest it could be an alternative to colonoscopy in the familial risk population, especially if the latter manages to significantly increase adherence to screening.

FIT efficacy in the familial risk population has been examined in several pilot studies, showing a sensitivity ranging from 29-80% for detection of advanced adenoma and CRC, with a specificity of 87% and 96%, respectively [14,15]. The only prospective randomized clinical trial comparing FIT and colonoscopy efficacy in FDRs of patients with CRC, conducted by our group, showed that annual FIT is equivalent to colonoscopy for the detection of advanced colorectal neoplasia according to both per- protocol analysis (OR 1.56, 95% CI 0.95, 2.56) and intention-to-treat analysis (OR 1.41, 95% CI 0.88, 2.26) [16]. However, that study was not designed to analyze screening adherence to both tests. In addition, it did not allow the authors to discern whether FIT detection of advanced colorectal neoplasia in the entire familial risk population can be extrapolated to the higher risk subpopulation. Said

subpopulation consists of FDRs of CRC index cases <60 years old and persons with two or more relatives or at least one sibling diagnosed with CRC, regardless of age at diagnosis.

Approximately 70-80% of CRCs develop from a precursor lesion, the adenomatous polyp, following the 'adenoma-carcinoma sequence', such that the removal of these lesions by polypectomy prevents CRC mortality [17]. This represents a crucial advantage for screening as a preventive strategy that can detect and remove the lesion in the asymptomatic phase. However, one of the most significant advances in recent years in gastrointestinal oncology has been the identification of ‘serrated lesions’ as precursors of CRCs through the so-called ‘serrated pathway’ of carcinogenesis, responsible for up to 15-20% of all CRCs [18]. A recent study in Spain found that the overall prevalence of serrated polyps in the intermediate risk population is 20.8%, 6.5% located in the proximal colon and 1.8% greater than 10 mm [19]. These polyps feature a flat morphology, usually located in the right colon and are often covered with mucus, so their detection is difficult and requires a high level of suspicion and adequate colon cleansing [18]. FIT is very reliable for the detection of CRC following the 'adenoma-carcinoma sequence "[13]. However, its diagnostic accuracy for the detection of serrated polyps with increased risk of malignancy, especially sessile serrated polyps, traditional serrated polyps, and hyperplastic polyps larger than 10 mm, is unknown. Furthermore, prevalence of serrated polyps and their role in colorectal carcinogenesis in the population at high familial risk is unknown. The population at high familial risk consists of: FDRs of individuals with an index case when less than 60 years old, persons with two or more relatives with CRC and persons with at least one sibling diagnosed with CRC, regardless of age at diagnosis.

Finally, CRC screening by annual or biennial FIT, sigmoidoscopy every 5 years or colonoscopy every 10 years is cost-effective in the intermediate-risk population [20]. However, there are no data on cost- effectiveness of these methods in the familial risk population from the perspective of healthcare services and society.

Therefore, the hypothesis of this study is that annual screening by FIT can substantially improve adherence to CRC screening in the population at high familial risk with a similar diagnostic efficiency to colonoscopy. With these assumptions, we propose the implementation of a pragmatic study comparing adherence, diagnostic efficacy and cost-effectiveness using annual FIT screening compared to colonoscopy in FDRs at high risk of developing CRC.

### 3. OUTCOMES

Primary outcome: to compare screening uptake of annual fecal immunochemical testing (FIT) versus one-time colonoscopy in individuals with a high-risk family history of non-syndromic CRC.

Secondary outcomes: a) to compare the efficacy of annual FIT vs one-time colonoscopy for detecting advanced colorectal neoplasia (ACN: advanced adenoma, advanced serrated polyp or CRC) in this population. b) to determine the cost-effectiveness of both strategies.

### 3. RESEARCH METHODOLOGY.

#### Study Design:

Multicentre, open-label, parallel group, randomized controlled clinical trial.

**Scope**: The study will be conducted in 7 autonomous communities: Aragon, Canary Islands, Catalonia, the Basque Country, Galicia, Madrid and Valencia.

Participating hospitals: Hospital Universitario de Canarias (Tenerife), Hospital Universitario de Donostia, Compleixo Hospitalario de Ourense, Compleixo Hospitalario de Pontevedra, Compleixo Hospitalario de Vigo, Hospital Universitario Puerta de Hierro, Madrid, Hospital Clinic de Barcelona, Hospital Universitario de Alicante, Hospital Universitario La Fe de Valencia, Hospital del Mar de Barcelona, and Hospital Universitario Lozano Blesa de Zaragoza.

### Target population.

#### Inclusion criteria:

Asymptomatic men and women with one or more FDRs (parents, siblings and children) with a history of CRC, who meet the following characteristics:

1. Asymptomatic individuals meeting one of the following conditions: a) having one index case of CRC diagnosed at <60 years old; b) having two FDR diagnosed with CRC, regardless of age at diagnosis; or c) having a sibling with CRC, regardless of age at diagnosis;
2. FDR over 40 years old or 10 years younger than the index case when diagnosed with CRC, if the index case was <50 years old.
3. Histologically confirmed CRC in the index case.

#### Exclusion criteria:

All individuals who meet the following conditions are to be excluded: 1) To have received previous CRC screening; 2) Personal history of inflammatory bowel disease (ulcerative colitis or Crohn's disease), prior colorectal adenoma or CRC; 3) Family history of familial adenomatous polyposis or hereditary nonpolyposis CRC; 4) Symptoms of colonic disease, such as rectal bleeding, recent change in bowel habits or significant weight loss; 5) Those who cannot undergo colonoscopy due to severe coagulopathy or for having undergone colectomy; 6) Those who have severe comorbidity with poor short-term prognosis (neoplastic disease with an average life expectancy of less than 5 years) or chronic disease with performance status greater than or equal to 2 (2: Self-employed but unable to work and is bedridden <50% of the day time, 3: Requires considerable assistance, frequent medical care and is bedridden >50% of the day time, 4: Is severely disabled and bedridden all the time); and 6) Those who decline to sign the informed consent.

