### Selection process and screening invitation.

It will be held on a scheduled basis from index cases diagnosed of CRC during the previous 24 months at the Endoscopy Units of participating centres. After at least 3 months from diagnosis and once radiotherapy or oncologic surgery have been performed, the index case will be contacted by phone to arrange an appointment at the High Risk CRC Clinic (HRCC). In this clinic the patient will be informed of the study objectives and informed consent and permission to contact their FDRs will be requested.

If the patient agrees to participate and meets the inclusion criteria, a family tree of the first generation (parents, children or siblings) will be generated to identify all eligible and living FDRs. At this point, an open-label randomization (1:1) for the subject and investigator, to FIT for three consecutive years and work-up colonoscopy if a positive test versus straightforward colonoscopy will be performed, using the randomization module in RedCap Electronnic Data Capture (REDcap). All individuals will receive a letter signed by the medical coordinator who saw the index case in each hospital. This letter will describe the importance of CRC as a health problem in the population at familial risk and will provide information of the next study in FDRs of patients with CRC (cover letter). Later, a second letter will be sent, also signed by the medical coordinator of the study, in which the individual will be invited to participate in the randomized control study (invitation letter). The study aim and the screening option to which the individual has been assigned will also be included in this second letter. Finally, a phone number or email will be provided to request a visit to the HRCC of the corresponding hospital. Individuals who do not respond to the invitation letter after 2 months will be sent a second invitation letter.

Eligible FDRs that attend the HRCC to participate in the study will receive detailed information on the advantages and disadvantages of both tests. Participants with a negative FIT result will be sent an invitation letter to repeat the test. Crossover between groups will not be allowed.

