### Statistical analysis plan

Screening uptake and detection rate of advanced neoplasia will be assessed by intention-to-screen analysis. First-degree relatives who will not attend the initial appointment and thus do not provide information about exclusion criteria will be considered as eligible and will be included in the analysis. Non-compliers for the assigned strategy will not be allowed to change to the other group. Between- group comparisons of the main outcomes will be calculated by multivariable logistic-regression analysis with adjustment for age, gender, and centre, and results were reported as odds ratios (OR) with 95% confidence intervals.

Comparisons of continuous variables were performed using the Mann–Whitney U-test. Categorical variables with two categories were compared using the χ^2^ test. All analyses were performed using SPSS statistical software version 25.0.

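### Relatives who decline consent after randomisation are listed for exclusion, which conflicts with the intention-to-screen analysis of uptake

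*Supplement*

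**What the plan says.** **Timing of randomisation.** The executive summary says "Randomization (1:1) will be performed before signing the informed consent to avoid selection bias". The section on selection process and screening invitation agrees. Once the index case has consented and the family tree has been drawn, there is "an open-label randomization (1:1) for the subject and investigator", and letters go to the relatives afterwards. A later sentence of the executive summary says something different: "In case of willingness to participate in the study, the FDR will be randomized to one of the following arms".

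**Disclosure of allocation.** Of the invitation letter, the same selection section says "The study aim and the screening option to which the individual has been assigned will also be included in this second letter". The relative must then ask for a visit. At that visit the pros and cons of both tests are explained, and crossover is not allowed.

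**Exclusion.** The last item of the exclusion criteria is "Those who decline to sign the informed consent". The list opens by saying that everyone who meets one of its conditions is to be excluded.

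**Analysis.** The statistical analysis plan says "Screening uptake and detection rate of advanced neoplasia will be assessed by intention-to-screen analysis". It continues: "First-degree relatives who will not attend the initial appointment and thus do not provide information about exclusion criteria will be considered as eligible", and keeps these relatives in the analysis. It does not mention relatives who attend and then decline.

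**Outcome.** The executive summary says "Screening uptake will be defined as the percentage of FDR who participate at least in one of the three FIT screening rounds" in the FIT arm, or who undergo colonoscopy in the other arm.

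**The concern.** Randomising before consent is the right design for a trial of uptake, because refusing the offered test is part of what is being measured. That protection is lost if people who refuse are taken out afterwards. A relative who attends and declines already knows the allocation and is by definition a non-uptaker. Excluding that relative therefore selects the denominator on the outcome, after randomisation and possibly at different rates in the two arms.

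The stray sentence in the executive summary adds to the difficulty. If randomisation really followed willingness to take part, uptake would be measured only among willing relatives, which is a different question from the one the trial asks.

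The primary comparison is at stake, and so is the interim result on which the trial was stopped (158/439 v 147/431, Amendment 1). The analysed set should be unambiguous.

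**Working it through.** **1. Following one relative through the text.**

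| Step | Section | Effect |
|---|---|---|
| Randomised at the family tree | Selection process | Belongs to an arm before any contact |
| Letter names the test | Selection process | Later decisions are made knowing the arm |
| Does not attend | Statistical analysis plan | Kept, counted as no uptake |
| Attends, declines consent | Exclusion criteria | To be excluded; no rule keeps this relative |

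The last two rows have the same outcome (not screened) but different treatment.

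**2. The plan's own figure.** Inputs from the sample size section and executive summary: 50% v 60%, two-sided alpha 0.05, power 90%, up to 5% loss, 538 per arm. The pooled-variance formula gives 519 per arm, or 519/0.95 = 546.3, so 547 after 5% loss. With continuity correction it gives 538 before any loss. The stated 538 is therefore reproduced closely enough, and the sample size arithmetic is not at issue here. Power at 538 per arm is 91.0%; at 511 per arm (5% lost) it is 89.6%.

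**3. Effect of dropping decliners.** Let u be true uptake among all randomised relatives in an arm, and d the share who attend and decline. Decliners contribute nothing to the numerator, so analysed uptake = u/(1 − d) and analysed size = 538(1 − d). The values of d are assumptions, since the documents give none. With u = 0.60 (FIT) and 0.50 (colonoscopy):

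| Declining, FIT/colonoscopy | Analysed uptake | Difference (points) | Power |
|---|---|---|---|
| 0%/0% | 60.0% v 50.0% | 10.0 | 91% |
| 1%/2% | 60.6% v 51.0% | 9.6 | 88% |
| 2%/5% | 61.2% v 52.6% | 8.6 | 80% |
| 5%/10% | 63.2% v 55.6% | 7.6 | 68.5% |
| 5%/5% | 63.2% v 52.6% | 10.5 | 93% |
| 5%/2% | 63.2% v 51.0% | 12.1 | 98% |

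Example for 5%/10%: 0.60/0.95 = 0.632 and 0.50/0.90 = 0.556, with 511 and 484 analysed. Power in the last row is power to detect an exaggerated difference, so it is not a gain.

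**4. No true difference.** With 35% uptake in both arms and 5%/10% declining, analysed uptakes are 0.35/0.95 = 36.8% and 0.35/0.90 = 38.9%. This is a spurious 2.0 points in favour of colonoscopy, and the two-sided rejection rate is about 10% instead of 5%.

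**5. Eligibility checked only in attenders.** Prior screening or symptoms may come to light only at the visit, while non-attenders are presumed eligible. If a share q of attenders is ineligible and removed, and attendance equals uptake p, analysed odds = (1 − q)p/(1 − p). The factor (1 − q) cancels from the odds ratio when q is the same in both arms. With p = 0.60 v 0.50 the true odds ratio is 1.50. It stays 1.50 for equal q, becomes 1.33 for q = 20% (FIT) v 10% (colonoscopy), and 1.69 with these reversed. Absolute uptake is understated in every case.

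**The case against.** The strongest reply is that the plan specifies intention-to-screen, that the sentence on non-attenders only clarifies that rule, and that the exclusion list governs enrolment rather than the analysis set. On that reading a decliner already counts as a non-participant. Part of this stands: the analysis plan does not say that non-attenders are the only relatives kept, and the futility section calls the 870 relatives randomised. But the exclusion list is worded without such a limit, and the plan's reason for keeping non-attenders is that they provide no information on exclusion criteria. That reason does not cover someone who attended. Amendment 1 describes the same 870 as recruited, so the documents do not show which reading was applied.

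A reader might go further and infer that the exclusion inflates colonoscopy uptake, biases the comparison towards no difference, and so contributed to the futility stop. The documents do not support that. Relatives put off by colonoscopy can simply not reply to the letter, and they are kept as no uptake. A FIT-allocated attender who hears about both tests and prefers colonoscopy may also refuse, which reverses the bias. The 5%/10% case is also demanding: with 50% taken up and 10% declining, one in six attenders in the colonoscopy arm (10/60) would refuse after asking for a visit with the test known.

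The objection to the eligibility filter largely stands. Randomisation balances true ineligibility, and the odds ratio is distorted only if the ineligible share among attenders differs by arm.

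**Conclusion.** The concern holds as a conflict within the plan. Taken as written, the exclusion criteria remove known non-uptakers after randomisation, and the analysis plan, which names intention-to-screen, does not put them back. This is more than a missing detail, because the written rule and the stated analysis give different denominators for the primary outcome.

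The consequence cannot be signed or sized from the documents. It ranges from slight (1%/2%: power 88%) through material (5%/10%: 68.5%) to an exaggerated difference when refusal is higher in the FIT arm. Equal refusal raises both uptakes and changes the contrast little. All these figures rest on assumed refusal rates, on the planning values of 60% v 50%, and on 538 per arm before any other loss. Whether decliners were in fact left out of the 870 is not shown. Eligibility checking confined to attenders is a secondary matter that a sensitivity analysis can cover.

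**What to change.** 1. In the exclusion criteria and the statistical analysis plan, state that declining consent bars study procedures but does not remove a randomised relative from the analysis. Such relatives count as no uptake in their allocated arm.
2. Report post-randomisation exclusions by arm and reason. Add a sensitivity analysis of all randomised relatives with no post-randomisation exclusion. This also covers eligibility being checked only in attenders.
3. Correct the executive summary sentence that places randomisation after willingness to take part, so that it agrees with the selection section.

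The main analysis should not be limited to exclusions known from the index case. That would keep relatives found at the visit to be ineligible and would change the target from uptake among eligible relatives.

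The cost is minor wording changes and one extra analysis. Decliners need only minimal data (allocation, age, sex and no uptake), used where ethics approval permits, since an explicit refusal is not the same as not replying. Reported uptake may be somewhat lower.
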